## Abstract

Supplemental Digital Content is available in the text

## Introduction

1

Knee osteoarthritis (KOA) is a common chronic knee disease, with pain and limited function as the main causes.^[1,2]^ More than 9,000,000 people have been diagnosed with KOA through clinical and imaging methods in USA.^[3]^ In China, 19.4% of the elderly population more than 60 years of age suffer from KOA.^[4,5]^ According to the Bulletin of the World Health Organization, osteoarthritis is predicted to be the fourth leading cause of disability by 2020.^[6]^ Patients often have symptoms such as pain and dysactivity, which limits the mobility of patients, cause psychosocial problems such as low self-efficacy and depression, and decreases the quality of life.^[7,8]^ The current therapeutic for KOA were mainly aimed to reducing pain and improvement of joint mobility.^[9,10]^

According to the recent guidelines, knee replacement surgery was the only effective pain management approach for the end-stage KOA.^[11,12]^ For the non-surgical treatment of KOA, pharmacological, non-pharmacological and alternative treatments were widely applied in the clinical practice.^[13]^ Among them pharmacologic treatments were the mostly widely adopted. For example acetaminophen, topical treatment, nonsteroidal, anti-inflammatory drugs (NSAIDs), COX-2 inhibitors, opioids and intra-articular cartilage-protective agents.^[14]^ However, long time taking anti-inflammatory drugs was associated with serious adverse reactions, such as digestive and renal impairment.^[15]^ A number of patients had to stop taking drugs for the side effects. Most patients are unwilling to receive routine treatment due to side effects, contraindications, and unsatisfactory relief of symptoms.^[16]^ while not all the patients are the ideal surgical candidates, some patients afraid of operation. Therefore non-invasive, safe and effective treatment options are in great demand for those patients to improve symptoms.

Chinese medicine has been used to manage osteoarthropathy for thousands of years. Yuanhu Zhitong dropping pills were also applied for treat KOA. However its efficacy and security has not been reported in the literature. The purpose of this study is to assess the efficacy and security of Yuanhu Zhitong dropping pills for KOA, a large sample size and a reliable blind method will be used to draw a reliable conclusion.

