### Study design

2.1

This study will be a single-blinded, randomized, and Diclofenac Sodium Sustained Release Capsules controlled trial. It will be performed at Gansu Provincial Hospital of Traditional Chinese Medicine, Lanzhou, China. The project was evaluated and approved by the Research Ethics Committee of Gansu Provincial Hospital of Traditional Chinese Medicine (Ethical batch No. FJ/04-IRB/C/018-V3.0, Ethics Review Adoption Form places in the Supplemental Digital Content). We planned to begin recruiting patients from July 2019, Patients with stage I, II, and III knee osteoarthritis will be recruited. In this study, there will be 8 investigators. Including 1 chief orthopedic physician, 5 orthopedic physicians, 2 outcome assessors. Five orthopedic physicians will recruit patients. The included patients should meet the inclusion criteria and will introduce the patient to the trial process. The 5 orthopedic physicians will also tell the participants possible benefits and risks.

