### Sample size calculation

2.4

Preliminary estimates put the number of cases in each group at 25. Considering the influence of shedding and elimination (20%), the overall sample size was set as 60 cases, 30 cases in the experimental group and 30 cases in the control group.

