### Randomization and allocation concealment

2.5

Sixty patients will be divided into Yuanhu Zhitong dropping pills and Diclofenac Sodium Sustained Release Capsules groups with a ratio of 1:1, random number table will be used for divide the groups. Only the chief orthopedic physicians will be allowed to know the differences of the groups.

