#### Primary outcomes pain^[18,19]^

2.8.1

When the patient takes the medicine, it will be recorded as the first day. Patients will mark on a 100 mm visual analogue scale to assess the pain of their knee (from no pain to severe). At the end of 1, 2, 3, and 4 week, patients themselves and the assessors will record it.

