### Statistical analysis

2.11

All data collected during the study will input into SPSS 21.0 statistical software for statistical analysis. Among them, the counting data are expressed in the form of number of individuals and percentage (%). The measurements are expressed in the form of mean and standard deviation (X ± S), and processed by non-parametric test or paired *t* test of 2 related samples. In the statistical results, if *P* < .01, there was a significant difference in the cue data, if *P* > .01, there was no significant difference in the cue data.

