## Discussion

4

The results showed that the Yuanhu Zhitong Drop Pill group was superior to the Western medicine group in terms of VAS scores, WOMAC scale assessment results, patient satisfaction, and gastrointestinal symptoms assessment scale (GSRS scale),^[22]^*P* < .05, adverse reactions. The number of cases was significantly less than that of the western medicine group. This shows that Yuanhu Zhitong drop pills can effectively relieve limb pain without side effects, can improve the quality of life of patients, and has a significant effect.

In recent years, with the continuous development of traditional Chinese medicine research, it has achieved significant results in the treatment of knee osteoarthritis. At the same time, with its unique advantages such as multiple targets for therapeutic effects and low toxic and side effects, it has obtained a large number of patients and doctors. There are still many deficiencies in the research of traditional Chinese medicine for knee osteoarthritis. There are some limitations with this study. First, the sample size of this study is small and it is a single-center randomized controlled study. Second, patients using VAS scores are too subjective. Third, a large number of clinical studies lack long-term efficacy. The safety of the drug need long time to observe.

Therefore, large-scale randomized double-blind controlled experiments should be carried out in future clinical research to strive for innovative and prospective related studies with rich center points and large sample sizes. In conclusion, we hope that the results of this study can provide new evidence for the treatment of early knee osteoarthritis pain with traditional Chinese medicine.

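### The aim is the efficacy of Yuanhu Zhitong, but the only control is active diclofenac, no comparative question is set, and the named analysis is within-patient

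*Protocol article*

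**What the plan says.** All references are to the Protocol article.

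- **Section 1, Introduction.** On the test drug: "However its efficacy and security has not been reported in the literature". The aim follows: "The purpose of this study is to assess the efficacy and security of Yuanhu Zhitong dropping pills for KOA". It names no comparator and no direction.
- **Section 2.1, Study design.** "This study will be a single-blinded, randomized, and Diclofenac Sodium Sustained Release Capsules controlled trial".
- **Section 2.5, Randomization and allocation concealment.** "Sixty patients will be divided into Yuanhu Zhitong dropping pills and Diclofenac Sodium Sustained Release Capsules groups with a ratio of 1:1". No placebo or untreated arm is described.
- **Section 2.4, Sample size calculation.** "Preliminary estimates put the number of cases in each group at 25". This is raised for 20% loss to 30 per arm, 60 in all. No effect, SD, power, significance level or margin accompanies it.
- **Section 2.8.1, Primary outcomes.** Knee pain on a 100 mm VAS, marked by the patient, at the end of weeks 1 to 4.
- **Section 2.11, Statistical analysis.** Measurements are to be handled by a non-parametric test or a paired t test for two related samples. P below .01 is a significant difference. Above .01, "there was no significant difference in the cue data".
- **Section 4, Discussion.** After reporting that the test arm did better than the Western medicine arm on VAS and other scales at P < .05, it concludes: "This shows that Yuanhu Zhitong drop pills can effectively relieve limb pain".

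**The concern.** In a two-arm trial with an active control, randomisation protects one thing: the contrast between the arms. A question about whether the drug works has to be answered through that contrast. Either the drug beats diclofenac, or it is shown to be no worse by more than a margin justified in advance. The visible text sets neither question.

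The analysis that section 2.11 does fix points elsewhere. A paired test compares patients with themselves over time. Patients enter after two weeks without medication (section 2.2), have a chronic painful condition and rate their own pain, so both arms may improve over four weeks through natural course and expectation alone. The other result the section provides for is a P value above .01, which in a trial of this size says little about whether the two drugs perform alike.

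At stake is the trial's headline conclusion. The Introduction says there is no reported efficacy for this drug, so nothing can be borrowed from earlier studies to fill the gap.

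**Working it through.** **1. The plan's own figure.** The 25 per group cannot be reproduced, because none of its inputs is given. The allowance for loss can: 25 × 1.2 = 30 per arm, 60 in all. (Dividing instead gives 25 / 0.8 = 31.25, so 32 per arm.)

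Nor does the figure reveal the intended question. In the normal approximation n = 2(z₁ + z₂)² / d², with d = 0.8 SD, z₁ = 1.960 and z₂ = 0.842 (80% power):

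n = 2 × 2.802² / 0.64 = 24.5, so 25.

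The same result follows for superiority by 0.8 SD at two-sided .05 and for non-inferiority with a margin of 0.8 SD at one-sided .025 and a true difference of zero. The article states neither.

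**2. What a null result leaves open.** Inputs: 25 evaluable per arm (section 2.4); the .01 level (section 2.11); SDs of 15 and 20 mm for week-4 VAS, which are assumptions.

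Half-width = t(48) × SD × √(2/25), with √(2/25) = 0.2828, t = 2.011 for 95% and 2.682 for 99%.

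| SD (mm) | Standard error (mm) | 95% half-width (mm) | 99% half-width (mm) |
|---|---|---|---|
| 15 | 4.24 | 8.5 | 11.4 |
| 20 | 5.66 | 11.4 | 15.2 |

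At the plan's .01 level, an observed difference of zero is compatible with the test drug being more than 10 mm worse than diclofenac, in patients who enter below 60 mm. At the 95% level with SD 15 mm, an interval centred on zero would exclude 10 mm.

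Put as a probability (noncentral t, two-sample test, 25 per arm): if the drug were truly worse by 0.5 SD, P > .01 would still occur in 81% of trials; if worse by 0.8 SD, in 44%. These true differences are assumptions.

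**3. What a within-arm test shows.** Suppose an arm improves for reasons unrelated to the drug. With 25 patients, a paired t test at .01 would be significant in 40% of trials if that shift were 0.5 SD of the change score, and in 87% if it were 0.8 SD. The shifts are assumed. The test cannot separate them from a drug effect.

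**4. What 25 per arm can detect.** Detectable difference at 80% power = (z₁ + 0.842) × 0.2828.

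- Two-sided .05: 2.802 × 0.2828 = 0.79 SD, or 11.9 to 15.8 mm at SD 15 to 20 mm.
- Two-sided .01: 3.418 × 0.2828 = 0.97 SD, or 14.5 to 19.3 mm.

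**5. If non-inferiority were chosen.** With an illustrative margin of 10 mm, one-sided .025, 80% power and no true difference, 36 per arm (SD 15 mm) to 63 per arm (SD 20 mm) are needed before loss, against 25 planned.

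**The case against.** **The article is condensed.** A full protocol or analysis plan may state a hypothesis and a margin. This stands as a limit: their absence can be asserted only of the visible text. It does not remove the point, because the article is not silent on analysis. It names a related-samples analysis and a two-way rule on P. One could read the non-parametric test as not confined to related samples, but even so no between-arm test is named.

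**The comparison is obvious.** The trial is randomised 1:1 against diclofenac, and an aim of assessing efficacy is ordinary introductory wording. That is fair, and the lack of a placebo arm is not in itself an error. An obvious comparator still does not say whether the question is superiority or non-inferiority.

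**A reader might infer that the authors mean to present a null result, or a fall in VAS within an arm, as proof of efficacy.** The article does not say so. No passage calls the drugs equivalent or says that within-arm change will count as efficacy. The defect is that the plan as written yields these results and does not bar that reading.

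**A reader might infer that the efficacy statement in the Discussion rests on within-arm change.** It does not. It follows a claimed between-arm advantage, which is a valid route to efficacy. Its fault is that a protocol has no results to support it. The claimed advantage also cannot serve as the missing hypothesis: it is worded as a result, at .05 where section 2.11 sets .01.

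**A reader might cite regression to the mean.** Entry VAS is bounded at both ends, above 10 and below 60 mm, so its direction is uncertain. The argument needs only natural course and expectation.

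**Conclusion.** The point holds in this form: an efficacy aim, an active control only, no comparative hypothesis or margin in the visible text, and a named analysis that leads to within-arm change or to an uninterpretable null. Neither shows that the drug works. A superiority result over diclofenac, specified in advance, would.

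The imprecision behind a null is 11.4 to 15.2 mm either side at the 99% level with 25 per arm. It rests on assumed SDs of 15 to 20 mm and would scale in proportion to the true SD. The argument about design does not depend on those SDs.

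The documents do not settle whether the question should be superiority or non-inferiority; that choice is the sponsor's. The point must be corrected before analysis because it decides what the trial may conclude.

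**What to change.** 1. In sections 1, 2.1 and 2.11, restate the objective as a comparison of Yuanhu Zhitong with diclofenac on VAS pain.
2. In section 2.11, replace the related-samples test as the primary analysis with a two-independent-sample analysis. Report the between-arm VAS difference with its confidence interval as the primary result.
3. State that only demonstrated superiority over diclofenac will support an efficacy claim. If the sponsor prefers non-inferiority, a margin must be justified in advance and the sample size derived from it; the present size may not support one.
4. State that within-arm change is descriptive, and that P above the threshold is not evidence of equivalence or effectiveness.
5. Remove the efficacy conclusion from section 4.
6. State as a limitation that 25 evaluable per arm is likely to detect only a large difference: about 0.79 SD at .05 or 0.97 SD at .01, with 80% power.

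**Cost.** These edits change wording and the primary analysis; they add no visits and in themselves no patients. The price is a narrower claim if superiority is not shown, and a real chance of that outcome. Detecting a 10 mm advantage with 80% power at SDs of 15 to 20 mm would take 36 to 63 per arm at .05, or 53 to 94 at .01, before loss. Enlarging the trial is a separate decision for the sponsor.

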## Methods

2

### Study design

2.1

This study will be a single-blinded, randomized, and Diclofenac Sodium Sustained Release Capsules controlled trial. It will be performed at Gansu Provincial Hospital of Traditional Chinese Medicine, Lanzhou, China. The project was evaluated and approved by the Research Ethics Committee of Gansu Provincial Hospital of Traditional Chinese Medicine (Ethical batch No. FJ/04-IRB/C/018-V3.0, Ethics Review Adoption Form places in the Supplemental Digital Content). We planned to begin recruiting patients from July 2019, Patients with stage I, II, and III knee osteoarthritis will be recruited. In this study, there will be 8 investigators. Including 1 chief orthopedic physician, 5 orthopedic physicians, 2 outcome assessors. Five orthopedic physicians will recruit patients. The included patients should meet the inclusion criteria and will introduce the patient to the trial process. The 5 orthopedic physicians will also tell the participants possible benefits and risks.

### Participants

2.2

The following eligibility criteria apply to all patients for recruitment into the study. Patients will be recruited through the Orthopaedics clinic of Gansu Provincial Hospital of Traditional Chinese Medicine. After oral explanation and reading of the procedures used in the study, patients agreeing to participate will sign an informed consent form.

Inclusion criteria:

1.Aged 45 to 70 years;2.Meet the diagnostic criteria for knee osteoarthritis according to American Rheumatism^[17]^ Association guidelines;3.Visual analogue scoring (VAS) is more than 10 mm and less than 60 mm;4.Patients with stage I, II, and III knee osteoarthritis;5.No medication has been taken in the past 2 weeks.

Exclusion criteria:

1.Undergone knee surgery;2.traumatic osteoarthritis;3.Pregnant and lactating women;4.Unable to attend the follow-up within 1 month;5.Complicated with liver, kidney, hematopoietic system, digestive system, cardiovascular and cerebrovascular diseases, and other serious primary diseases;6.Tuberculosis of knee joint, deformity of knee joint, and malignant tumors of knee joint;7.Psychiatric diseases and can not cooperation;8.Opioid analgesics, sedatives and hypnotics, and alcohol abuse;9.Allergy to experimental drugs.

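### The tests named in section 2.11 adjust for neither baseline VAS nor KOA stage, although both are known at entry; precision may be lost and a chance stage imbalance would stay unadjusted

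*Protocol article*

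**What the plan says.** - **Eligibility (2.2 Participants).** Three disease stages are admitted: "Patients with stage I, II, and III knee osteoarthritis". Entry pain is bounded by another criterion: "Visual analogue scoring (VAS) is more than 10 mm and less than 60 mm". Both values must be established before a patient can be enrolled.
- **Allocation (2.5).** Sixty patients are allotted to "groups with a ratio of 1:1", and a "random number table will be used for divide the groups". No strata, blocks or minimisation are named.
- **Primary outcome (2.8.1).** "Patients will mark on a 100 mm visual analogue scale to assess the pain of their knee", at the ends of weeks 1 to 4.
- **Analysis (2.11).** Continuous measurements are "processed by non-parametric test or paired *t* test of 2 related samples". The threshold is stated as "if *P* < .01, there was a significant difference in the cue data". No covariate or stratum is mentioned.

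Stage is not mentioned again after eligibility.

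**The concern.** Stage and starting pain are natural candidates for predictors of pain at week 4, and both come free with the eligibility check. A comparison that ignores them leaves whatever they explain in the error term. It also leaves any chance difference in case mix between two arms of 30 inside the estimate. Baseline VAS need not stand in for stage: the same VAS window applies to all three stages, and stage could also bear on response.

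Two things are at stake. One is precision, in a trial that plans about 25 evaluable patients per arm and demands P < .01. The other is how a result will be read if the arms turn out visibly different in stage. Without a prespecified adjustment, any adjusted analysis would then be chosen after the imbalance had been seen.

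**Working it through.** **Inputs from the article.** 25 evaluable per group, 20% loss, 30 per group and 60 in total (2.4); 1:1 allocation (2.5); threshold .01 (2.11). I also show .05, because the Discussion uses it.

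**Inputs not in the article (assumptions).** Stage mix; effect of 0.8 SD; two-sided testing; R², the share of week-4 VAS variance that stage explains over and above baseline VAS.

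**1. The plan's own sample size.** 25 × 1.20 = 30 per group, 60 in total, which reproduces. Losing 20% of 30 leaves 30 × 0.80 = 24 per arm, the number used in step 4. The base figure of 25 cannot be checked, because no effect size, SD or power is given.

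**2. How likely is a stage imbalance?** Let X be the number of stage III patients in one arm of 30, hypergeometric from 60.
- With 20 stage III patients: P(13:7 or worse) = P(|2X − 20| ≥ 6) = 0.170; P(12:8 or worse) = 0.412.
- A difference of at least 20 percentage points between arms has probability 10%, 17% or 20% if stage III makes up 20%, 33% or 50% of patients.
- A difference of at least 30 points has probability of about 0.2% to 2%.

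**3. What does an imbalance do to an unadjusted two-sample t test?** Simulation with 25 per arm, stages equally frequent and 40,000 runs for each R² (0.10, 0.20, 0.30).
- Over all randomisations the rejection rate under no effect is 0.9% to 1.1% at nominal 1%, and 4.8% to 5.1% at nominal 5%. The test keeps its level.
- A difference in mean stage of at least 0.4 occurs in about 9% of trials. A difference of exactly 0.4 shifts the estimate by 0.4 × √(R² ÷ (2/3)) = 0.15, 0.22 and 0.27 SD at R² = 0.10, 0.20 and 0.30.
- Given a difference that large or larger, the false-positive rate at nominal 1% is about 1.6%, 3.8% and 5.3%.

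**4. What does adding stage do to power?** With n = 24 per arm:
- Without stage, the noncentrality is 0.8 × √(24/2) = 2.771 on 46 df. Power is 77.4% at .05 and 53.8% at .01.
- With stage, the residual variance is multiplied by (1 − R²). Estimating two stage terms costs 2 df and multiplies the variance of the arm effect by about 1 + 2/(48 − 5) = 1.0465.
- The noncentrality becomes 2.771 ÷ √[(1 − R²) × 1.0465] on 44 df. At R² = 0.10 this is 2.856.

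| Assumed R² | Power at .05 | Change (points) | Power at .01 | Change (points) |
|---|---|---|---|---|
| 0 | 75.5% | −2.0 | 51.2% | −2.6 |
| 0.05 | 77.6% | +0.2 | 53.9% | +0.1 |
| 0.10 | 79.8% | +2.3 | 56.8% | +3.0 |
| 0.20 | 84.2% | +6.8 | 63.3% | +9.4 |

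Changes are taken before rounding. Setting (1 − R²) × 1.0465 = 1 puts break-even at R² = 1 − 43/45 = 0.044, before the small further cost of the 2 df.

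In equivalent sample size, 1 ÷ [(1 − R²) × 1.0465] gives 0.96, 1.01, 1.06 and 1.19 for the four rows.

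The table isolates stage. The gain from baseline VAS is not quantified, because the article gives no correlation between baseline and week 4.

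**The case against.** The case against has four parts.

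- **Covariates belong in the SAP, which is not shown.** This would settle the matter had the article been silent on method. It is not: 2.11 names its tests, and they cannot use a covariate. The point is made against what is stated, not against missing detail.
- **The benefit is unproven.** This stands. A reader might infer that precision is certainly lost, by the equivalent of 5% to 25% of patients (1/0.95 to 1/0.80 at R² = 0.05 to 0.20). The article gives no association between stage and VAS and no stage mix. Those figures also leave out R² = 0 and the cost of estimating stage. Net of that cost, the range from R² = 0 to 0.20 is about −4% to +19%.
- **Chance imbalance is not an error.** This also stands. A reader might infer that unstratified allocation biases the trial or inflates its type I error. Randomisation protects against both over all randomisations, as step 3 shows. The conditional error rates describe the minority of trials in which a large imbalance has occurred. Nor does the article support a claim that stratification is required at 60 patients.
- **A larger fault sits in the same sentence.** Agreed. A paired test on related samples does not compare two independent arms, so there is no clearly stated between-arm model for stage to enter. Adding stage to the paired test would repair nothing. The remedy has to replace the test, and the covariates can be set at the same time.

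**Conclusion.** The point holds as a minor one. The tests stated in 2.11 make no use of baseline VAS or KOA stage, both available at entry. A stage imbalance large enough to notice is plausible with 60 patients allocated without stated strata, and nothing in the stated analysis would adjust for it. Precision may be lost; the article does not allow the stronger statement that it is.

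At 24 per arm and 0.8 SD, the net effect of adding stage runs from a loss of 2 to 3 power points if stage has no prognostic value, through nothing at R² = 0.05, to a gain of 2 to 3 points at 0.10 and about 7 to 9 at 0.20. These sizes rest wholly on the assumed effect and R². The imbalance probabilities rest on an assumed stage mix. The downside is small and bounded, and the upside is moderate.

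**What to change.** In 2.11, make the primary analysis a between-arm ANCOVA of week-4 VAS on treatment arm, with baseline VAS (continuous) and KOA stage (I, II, III as categories) as prespecified covariates. Use the same model for WOMAC with its own baseline value. Leave the randomisation as planned.

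Two details should be settled in the same edit. State which pre-treatment VAS reading serves as baseline. Confirm that WOMAC is recorded before the first dose, since 2.8.2.1 lists it only at the ends of weeks 1 to 4.

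The cost is analysis wording, 2 degrees of freedom for stage and 1 for baseline VAS, and about 2 to 3 power points if stage proves to carry no information. If a pre-treatment WOMAC is not already planned, one questionnaire is added at entry.
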